**Figure 2 figure2:**
[figure not shown]
Study protocol.

### Outcome Measures and Assessment Points

Evaluations will be carried out before and after 8 weeks of intervention and the 12- and 24-week follow-ups. Individuals will be monitored weekly during the study period, and messages will be sent through WhatsApp (Meta Platforms) to collect information about pain intensity.

#### Primary Outcome Measure

The primary outcome measure will be a report of pain intensity on the Numerical Pain Rating Scale [17].

#### Secondary Outcome Measures

The secondary outcome measures will be as follows:

Comparison of disability outcomesScores measured by using the Roland Morris Disability Questionnaire [18]Comparison of physiologic and psychologic stressScore for the Fear Avoidance Belief Questionnaire [19]Score for the Tampa Scale of Kinesiophobia [20]Score for health-related quality of life from the Short Form-12 Health Survey Version 2 [21,22]Score for the Brunel Humor Scale [23]Scores measured by using the Beck Depression Inventory [24] and Beck Anxiety Inventory [25]Scores measured by using the Pittsburg Sleep Quality Index [26] for evaluating sleep quality and behavior

Any adverse effects that are observed or reported by the patients will be recorded and considered for the final study outcomes. Furthermore, patients who experience adverse effects will be sent to a physician for adequate treatment.

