### Pain Education

The educational program will be based on the protocol described by Traeger et al [16] and will consist of a biopsychosocial approach to dealing with fears and clarifying behavioral beliefs about pain and movement. Additionally, the program will explain the influence of emotional symptoms (stress, anxiety, kinesiophobia, etc) on chronic pain; the influence of lack of sleep and physical activity on LBP, gradual exposure to physical activity, and daily movements; and the neurophysiology of pain. The program will include the following three major components: (1) clarifying any useless beliefs about the nature of LBP, (2) presenting key concepts of the biology of pain, and (3) evaluating patients’ understanding and discussing recovery. Participants who are randomized to the pain education intervention will participate in two 1-hour sessions of pain education that will be conducted by a physiotherapist. The physiotherapist will be appropriately trained for the study and will be contacted weekly for clarifications on doubts and possible further guidance. Multimedia Appendix 1 shows the 3 steps of the Pain Education Program.

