#### Random Allocation and Blinding

After the initial evaluation, the participants will be allocated, through block randomization, to receive different interventions, which will be conducted by physiotherapists. Individuals who fulfill the inclusion criteria will receive clarification about the objectives and the procedures that will performed in the research, and their consent will be requested by asking them to sign the informed consent form, of which the terms were approved by the ethics committees of the Federal University of Pelotas and the Health Department of Pelotas City.

The participants will then be referred to the physiotherapist who will be selecting the interventions according to the groups to which the participants will be allocated. The individuals who are allocated to the M-group, MP-group, and U-group will participate in 16 treatment sessions (2 sessions per week, totaling 8 weeks of treatment) with an average duration of 40 minutes.

It will not be possible to blind the physiotherapists who are responsible for the interventions due to the type of research that will be conducted. However, evaluators and patients will be blinded to the treatment groups. Nonblinding conditions will only occur in cases of health emergencies.

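### Adverse effects may be under-recorded in the pain education arm, which has two sessions against 16 in the other three arms and no common adverse-effect enquiry described

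*Protocol article*

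**What the plan says.** The capture rule stands at the end of Secondary Outcome Measures in the protocol article: "Any adverse effects that are observed or reported by the patients will be recorded and considered for the final study outcomes". The next sentence there sends patients with adverse effects to a physician.

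Contact with treatment staff differs by arm. Random Allocation and Blinding states: "The individuals who are allocated to the M-group, MP-group, and U-group will participate in 16 treatment sessions", at two per week for 8 weeks. Under Pain Education, participants in that arm "will participate in two 1-hour sessions of pain education".

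Two kinds of contact are common to all arms. Under Outcome Measures and Assessment Points, "Individuals will be monitored weekly during the study period, and messages will be sent through WhatsApp (Meta Platforms) to collect information about pain intensity". The same section sets evaluations before treatment, after 8 weeks, and at 12 and 24 weeks.

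Two further weekly contacts are tied to particular programmes. Usual Care Intervention, in its paragraph on the exercise programmes, has researchers asking patients each week how the intervention is going. Pain Education has a contact in which someone "will be contacted weekly for clarifications on doubts and possible further guidance"; as the sentence is built, that someone is the physiotherapist, so it is unclear whether patients are reached.

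The Abstract and the Conclusions both say that the trial will give preliminary information on the safety of motor control exercises and of pain education.

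**The concern.** Whether an effect is observed depends largely on staff being with the patient. Whether it is reported depends on having an occasion to report and on being asked. Three arms offer 16 such occasions through treatment and the fourth offers two. The contact that could even this out, the weekly message, is described in terms of pain intensity.

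If the rule is followed as written, two arms with the same true risk can yield different counts. Study Design says that each of the three interventions will be set against usual care, so pain education versus usual care is a core contrast of the trial, and it is one that carries the imbalance. Safety data from a randomized four-arm trial will naturally be read by arm, and the reader would have no way to separate a milder intervention from a less closely watched one. Because referral to a physician follows from an effect becoming known, an effect that goes unnoticed may also go unreferred.

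**Working it through.** **Inputs from the protocol article**

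- Sessions in the motor control exercise (M), combined (MP) and usual care (U) arms: 2 per week × 8 weeks = 16. This reproduces the stated figure.
- Sessions in the pain education (P) arm: 2.
- Weekly contacts during the 8 treatment weeks, all arms: 8.
- Common assessments after baseline: 3 (8, 12 and 24 weeks).
- Arm size: 225 (Sample Size Calculation). Significance level: 0.05 (Statistical Analysis); two-sided assumed.

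**Contact counts**

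- Sessions only: 16 against 2, or 8 to 1.
- Sessions plus weekly contacts: 16 + 8 = 24 against 2 + 8 = 10, or 2.4 to 1.
- M : MP : U on sessions: 16 : 16 : 16. Only contrasts that involve P are unbalanced.

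**Model**

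Let p be the true risk of an adverse effect, equal in both arms, q the chance that it is recorded at any one contact, and k the number of contacts. Then

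recorded risk = p × [1 − (1 − q)^k].

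The ratio between arms is [1 − (1 − q)^k1] / [1 − (1 − q)^k2]; p cancels. The article gives neither p nor q, so both are assumptions. The model treats contacts as independent and gives every effect the full number of chances to be recorded, so it is an illustration and not a forecast.

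| q (assumed) | Sessions only, 16 v 2 | Ratio | With 8 weekly contacts capturing effects, 24 v 10 | Ratio |
|---|---|---|---|---|
| 0.05 | 0.560 v 0.098 | 5.74 | 0.708 v 0.401 | 1.76 |
| 0.10 | 0.815 v 0.190 | 4.29 | 0.920 v 0.651 | 1.41 |
| 0.20 | 0.972 v 0.360 | 2.70 | 0.995 v 0.893 | 1.11 |
| 0.30 | 0.997 v 0.510 | 1.95 | 1.000 v 0.972 | 1.03 |

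The paired entries are the share of *existing* effects that get recorded. They must be multiplied by p before they can be read as a share of patients.

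**The common assessments**

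If the three assessments captured effects as a session does, but the weekly contacts did not, the counts would be 16 + 3 = 19 against 2 + 3 = 5. At q = 0.05 the ratio is 0.623/0.226 = 2.75; at q = 0.30 it is 0.999/0.832 = 1.20. The assessments dilute the imbalance without removing it.

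**What it could do to a comparison**

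Take p = 0.20 in both arms and 225 patients per arm.

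- q = 0.10, sessions only: 0.20 × 0.815 = 16.3% against 0.20 × 0.190 = 3.8%. A two-sided 5% test would find a false difference with probability about 0.99.
- q = 0.10, weekly contacts also capturing: 18.4% against 13.0%; probability about 0.35.
- q = 0.30, weekly contacts also capturing: 20.0% against 19.4%; probability about 0.04, so no inflation.

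The result runs from a severe artefact to none. What decides it is whether the shared contacts ask about adverse effects, and how well each contact picks them up.

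**The case against.** The strongest case against has five parts.

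*No safety comparison is specified.* This stands. The article promises preliminary safety information; the Goal of the Study contains no safety contrast, and adverse effects are not among the outcomes listed under Statistical Analysis. A reader might infer that a promised between-arm safety comparison is already biased, but the article does not promise one. The point concerns how counts by arm could be read.

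*Silence is not a negative.* The article does not say that reports are unsolicited or that the weekly message asks about nothing but pain, and a fuller protocol may hold the procedure. This stands in part. It is why the conclusion is that effects may be under-recorded, not that they will be. But the capture rule, the session counts and the purpose of the message are all stated, and together they leave the pain education arm exposed.

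*Shared contacts reduce the imbalance.* This also stands in part. Weekly monitoring and the common assessments give every arm regular occasions to report. If they captured effects well, the ratio would come close to 1. Nothing in the article says that adverse effects are asked about on those occasions.

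*The scope is narrow.* This stands. Usual care also has 16 sessions, so a reader who infers that exercise will look worse than usual care merely through being seen more often would be mistaken.

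*Percentages of patients are easily overstated.* This stands. With a pick-up chance of 1% to 5% per contact, 1 − (1 − q)^k gives 15% to 56% for 16 sessions and 2% to 10% for two. A reader might take these as shares of patients with a recorded effect. That would be right only if every patient had an effect. At an assumed true risk of 10% they become about 1.5% to 5.6% and 0.2% to 1.0%.

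**Conclusion.** The point holds in a limited form. Under the stated rule, adverse effects may be under-recorded in the pain education arm, and that arm could look safer than usual care or either exercise arm with no true difference. Comparisons among the three 16-session arms are not affected.

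For equal true risk and an assumed 5% to 30% chance of recording per contact, the recorded-risk ratio of a 16-session arm to the pain education arm is about 5.7 to 2.0 on sessions alone, and about 1.8 to 1.0 if the eight weekly contacts also captured effects. These ranges rest on the assumed recording chance and on the simple contact model; the article supplies neither. The documents do not support the firmer statement that the safety results are biased by a known amount.

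**What to change.** Add one fixed adverse-effect question, worded identically for all four arms, to the weekly message and to the common assessments at 8, 12 and 24 weeks. Use these solicited answers for the main by-arm safety table. Report effects seen at treatment sessions in a separate table by arm, so that none are discarded and the two sources are not mixed. State under Secondary Outcome Measures that the main table rests on solicited answers, and make clear under Pain Education who receives the weekly contact.

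The cost is one question in a message that is already sent, one further question at three existing assessments, one extra table and a slight added burden for patients. Some patients will not answer the messages, and non-response could differ by arm, so response rates should be reported by arm beside the main table. No treatment rule changes.

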### Study Procedures

#### Sample Size Calculation

Sampling will be probabilistic, and patients will be extracted from the LBP waiting list. The required sample size was calculated by assuming a mean difference of 1.5 and an SD of 2.4 [27]; the study requires a sample size of 225 per group, that is, 900 individuals in total.

#### Random Allocation and Blinding

After the initial evaluation, the participants will be allocated, through block randomization, to receive different interventions, which will be conducted by physiotherapists. Individuals who fulfill the inclusion criteria will receive clarification about the objectives and the procedures that will performed in the research, and their consent will be requested by asking them to sign the informed consent form, of which the terms were approved by the ethics committees of the Federal University of Pelotas and the Health Department of Pelotas City.

The participants will then be referred to the physiotherapist who will be selecting the interventions according to the groups to which the participants will be allocated. The individuals who are allocated to the M-group, MP-group, and U-group will participate in 16 treatment sessions (2 sessions per week, totaling 8 weeks of treatment) with an average duration of 40 minutes.

It will not be possible to blind the physiotherapists who are responsible for the interventions due to the type of research that will be conducted. However, evaluators and patients will be blinded to the treatment groups. Nonblinding conditions will only occur in cases of health emergencies.

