### Data Collection

The professionals (physicians, nurses, physiotherapists, psychologists, and physical education professionals) from the health network of Pelotas City, Rio Grande do Sul, Brazil, will refer patients to the program after assessing their eligibility. Patients who show an interest in participating in the program will be marked for an initial evaluation, during which the patients will be informed about the research procedures, evaluations, interventions, and duration. After obtaining all of the necessary information, patients who wish to participate must sign the informed consent form. Only researchers will have access to the database. To maintain data confidentiality, patients will be identified by numbers.

The study protocol is shown in Figure 2. A baseline survey will be conducted after the allocation. Participants will receive questionnaires, including questions on demographic data and baseline data for outcomes.

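### The protocol states that patients are blinded, but the design cannot deliver this for any comparison with the pain education arm and hardly for the combined arm, so the self-reported primary outcome should be described as unblinded

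*Protocol article*

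**What the plan says.** The blinding statement is in Random Allocation and Blinding. On the therapists it is candid: "It will not be possible to blind the physiotherapists who are responsible for the interventions due to the type of research that will be conducted". It continues: "However, evaluators and patients will be blinded to the treatment groups". The next sentence makes clear that this is meant as a working condition of the trial: "Nonblinding conditions will only occur in cases of health emergencies".

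On what patients know beforehand, Data Collection says that at the initial evaluation "the patients will be informed about the research procedures, evaluations, interventions, and duration". Random Allocation and Blinding adds that eligible individuals "will receive clarification about the objectives and the procedures that will performed in the research".

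On what patients then receive:
- **M, MP and U:** "The individuals who are allocated to the M-group, MP-group, and U-group will participate in 16 treatment sessions", twice weekly for 8 weeks, about 40 minutes each.
- **P:** two 1-hour education sessions with a physiotherapist (Pain Education).
- **MP:** one hour of education at the first appointment, then the 8-week exercise programme (MCEs and Pain Education).

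On the outcome: "The primary outcome measure will be a report of pain intensity on the Numerical Pain Rating Scale". Pain intensity is also collected weekly from patients by phone message (Outcome Measures and Assessment Points). The instruments under Secondary Outcome Measures are questionnaires.

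**The concern.** Patients who have been told about the interventions and then receive education only, exercise only, or both will in most cases know which of these they have. The person who knows is also the person who rates the pain. An evaluator unaware of allocation then only records a rating made with knowledge of it.

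Expectation and attention can differ between arms and act directly on a pain score. They matter most where the arms differ most in content and contact, which is P against the exercise arms and the combined arm against its components. If the trial is reported as patient-blinded on the strength of this sentence, readers and risk-of-bias assessors will credit it with a protection that it does not have. Any statement about the most efficient intervention, which the Conclusions promise in preliminary form, would then be read with too much confidence.

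**Working it through.** **Step 1: the six pairwise comparisons.** Four arms give 4 × 3 / 2 = 6 pairs.

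| Pair | What the patient experiences | Can patient blinding hold? |
|---|---|---|
| P vs M | 2 education sessions vs 16 exercise sessions | No |
| P vs MP | education only vs education plus exercise | No |
| P vs U | 2 education sessions vs 16 exercise sessions | No |
| MP vs M | education hour plus exercise vs exercise only | Hardly |
| MP vs U | education hour plus exercise vs exercise only | Hardly |
| M vs U | two 16-session exercise programmes | Plausible, but no concealment described |

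Scheduled contact is 2 × 60 = 120 minutes in P and about 16 × 40 = 640 minutes in M and U. No sham or attention control is described.

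**Step 2: which planned comparisons this touches.** Study Design sets three interventions against usual care. Patient blinding fails for P vs U, is doubtful for MP vs U and is plausible for M vs U. The pooled pain contrasts in Goal of the Study (M and MP against P and U; P and MP against M and U) each contain P and MP, so neither escapes.

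**Step 3: who rates the outcome.** The patient rates the pain scale and completes the questionnaires. Evaluator blinding cannot change what the patient knows. The pressure pain threshold is taken with an algometer, so a blinded evaluator has less room to influence it. It still depends on the patient's response to pressure.

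**Step 4: an illustration of size.** The article gives no estimate of reporting bias, so I assume a between-arm bias b of 0.2 to 0.5 points with no true effect. Relative to the planned difference of 1.5, this is 0.2/1.5 = 13% to 0.5/1.5 = 33%.

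Inputs from the article: SD 2.4 and 225 per group (Sample Size Calculation), α 0.05 and Bonferroni post hoc tests (Statistical Analysis). Assumptions: two-sided tests, six pairs, a simple two-group comparison and no dropout.

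- Standard error: SE = 2.4 × √(2/225) = 0.226.
- Rejection probability: Φ(b/SE − z) + Φ(−b/SE − z), with z = 1.960 at 0.05 and z = 2.638 at 0.05/6.
- For b = 0.2, b/SE = 0.88. For b = 0.5, b/SE = 2.21.

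| Assumed bias b | Two-sided 0.05 | Bonferroni, 0.05/6 |
|---|---|---|
| 0 | 5% | 0.8% |
| 0.2 | about 14% | about 4% |
| 0.5 | about 60% | about 33% |

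I take the 225 per group as stated. A difference of 1.5 with SD 2.4 needs only 41 per group at 80% power or 54 at 90% (two-sided 0.05), so the inputs given do not reproduce 225. That is a separate matter. It is relevant here only because 225 per group can detect about 0.63 points at 80% power, which leaves a modest bias enough room to reach significance.

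**The case against.** The strongest defence concerns M against U. Both arms have 16 sessions of the same average length. Both train the transverse abdominis and multifidus, and usual care may also include advice to stay active. A patient in either arm might well not know which programme is experimental. This stands. A reader might infer that all four arms are visibly different, and the article does not support that. It does not rescue the other five comparisons, and the article describes no step that would keep M and U patients unaware.

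A second defence is that the consent text is not shown. The article says that interventions, objectives and procedures are explained. It does not say that all four arms are named or that patients are told their group. A reader might infer that the consent procedure by itself rules out blinding, which is more than can be shown. The argument rests mainly on the difference in what patients receive.

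Third, the article nowhere calls the primary outcome blinded, and its sentence on the most efficient intervention speaks of preliminary data and does not appeal to blinding. That is correct. The error is in the statement about who is blinded, and its consequence for the pain score is an inference from how that score is obtained. All participants are also monitored weekly, which narrows the attention gap slightly.

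Finally, it would be tempting to quote the 60% alone. It is the top of an assumed range without the multiplicity adjustment that the article specifies, so the whole range of about 4% to 60% has to be shown.

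**Conclusion.** The patient-blinding statement is wrong as written. It cannot hold for the three comparisons with P and is hard to defend for MP against M or U. It is plausible only for M against U, where nothing is described to secure it. The pain score and the questionnaires are therefore unblinded in most comparisons, whatever the evaluator knows.

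This conclusion rests on the session content and the self-reported outcome and needs no numerical assumption. The rejection rates (about 14% to 60% unadjusted, about 4% to 33% with Bonferroni over six pairs) depend wholly on an assumed bias of 0.2 to 0.5 points and do not show that such a bias will occur.

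A reader might also infer that the pressure pain threshold can serve as the blinded outcome. The same reasoning prevents this, because it too depends on a patient who knows the treatment received. Nor does the point show that the trial's design or analysis is unsound: participants often cannot be blinded in trials of exercise and education. The defect is that a protection is claimed that the design does not provide. The statement should be corrected.

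**What to change.** Replace the sentence in Random Allocation and Blinding with: *Evaluators are blinded to allocation; treating physiotherapists and participants are not.* Adjust the following sentence on emergency unblinding so that it refers to evaluators only.

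Then add three statements:
1. Exactly what, if anything, is withheld from participants. It must agree with the information promised in Data Collection and in Random Allocation and Blinding. A statement that the hypotheses are withheld, for example, would have to be reconciled with the promise to explain the objectives.
2. That the pain scale and the other self-reported outcomes are unblinded, and that conclusions about the most efficient intervention are qualified accordingly.
3. That the pressure pain threshold is supportive, with reduced assessor influence, and is not a blinded outcome.

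If the registry entry repeats the claim of patient blinding, it should be corrected as well. The cost is a change of wording and a less favourable stated level of blinding. Arms, sample size and analysis stay as they are.
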